## Abstract

**Introduction:**

Parkinson’s disease (PD) can be categorized into various subtypes based on the primary symptoms associated with motor dysfunction. One subtype, known as postural instability and gait difficulty (PIGD), is characterized by severe clinical symptoms, an increased risk of walking difficulties and falls, and a poorer prognosis compared to other subtypes. This condition imposes a significant burden on patients, their families, and the healthcare system. Recently, acupuncture, a practice rooted in traditional Chinese medicine, has gained attention for its potential to influence neurophysiological pathways and enhance the overall brain function in individuals with PD. This randomized controlled study aimed to evaluate the clinical effectiveness of acupuncture in patients with the PIGD subtype of PD and to investigate the preliminary exploration of mechanisms of acupuncture by analyzing intestinal microbiota and metabolomics, thereby providing deeper insights into its impact on patients.

**Methods:**

This randomized controlled trial will involve 64 patients diagnosed with the PIGD subtype of PD. Participants in both groups will undergo three acupuncture sessions weekly for a duration of 4 weeks, followed by an 8-week follow-up period. The primary outcome measure will be the Unified Parkinson’s Disease Rating Scale III. Secondary outcomes will include the Berg Balance Scale (BBS), wearable gait analysis, and functional magnetic resonance imaging (fMRI). Additionally, serum and stool samples will be collected for 16S ribosomal RNA sequencing, and liquid chromatography coupled with tandem mass spectrometry analysis (LC–MS/MS) will be employed to elucidate theunderlying mechanisms. This trial has been reviewed and approved by the Medical Ethics Committee of Zhejiang Hospital (Approval no. 2023-15 K). Participation in this study will require written informed consent from all patients. The findings of this study will be published in a peer-reviewed journal, and there will be no restrictions on publication.

**Discussion:**

In this study, we integrate traditional assessment scales with fMRI to demonstrate the therapeutic effects of acupuncture. We will also analyze the modulation of gut microbiota and serum metabolome to explore the underlying neural mechanisms. Our results will provide a foundation for future studies in this area.

**Clinical trial registration:**

https://www.chictr.org.cn, identifier ChiCTR2300071703.

## Introduction

1

Parkinson’s disease (PD) is a prevalent neurodegenerative disorder resulting from a complex interaction of genetic, environmental, and lifestyle factors (Poewe et al., 2017). There are various clinical manifestations of PD, including tremor-dominant (TD), postural instability and gait difficulties (PIGD), and the mixed type. Among these, the PIGD subtype presents particular challenges, as it often leads to significant motor impairment and a decreased quality of life for both patients and their families (Stebbins et al., 2013; Hattori, 2016; Tysnes and Storstein, 2017). Patients with the PIGD subtype are more susceptible to severe symptoms, frequent falls, and poorer prognosis than those with the TD subtype, thereby increasing the burden on caregivers and the healthcare system (Pelicioni et al., 2018; Pelicioni et al., 2019). Current treatment strategies often yield suboptimal results for the PIGD subtype; hence, complementary approaches such as acupuncture are suggested to potentially alleviate PD symptoms and improve patients’ overall wellbeing (Ahrweiller et al., 2019; Shin et al., 2020).

Acupuncture, a traditional Chinese practice, has demonstrated potential benefits in alleviating both motor and non-motor symptoms of PD (Xu et al., 2020; Lei et al., 2023; Li et al., 2023). In contrast to previous studies that primarily relied on scale recordings, our trial will employ advanced methodologies, including wearable gait analysis and functional magnetic resonance imaging (fMRI) assessments, alongside a multimodal approach to understanding the underlying mechanisms. These methodologies will be used to clarify how acupuncture enhances gait and brain function and explore its preliminary mechanisms of action and clinical benefits, particularly in individuals with the PIGD subtype.

Recent studies have indicated that the gut-brain axis significantly influences PD pathology and correlates with disease severity (Liu et al., 2024). Acupuncture has been employed to enhance brain function and mitigate inflammation in neurological diseases including PD, while also addressing gastrointestinal dysfunction in various gastrointestinal disorders (Zhang et al., 2023). By investigating the gut microbiome and its metabolites, researchers can gain insights into how acupuncture impacts the gut-brain axis and PD pathology. This comprehensive approach could provide a thorough understanding of the therapeutic effects of acupuncture and identify potential biomarkers or targets for future interventions (Jia et al., 2012; Fathi et al., 2013).

In summary, we will conduct a randomized clinical trial to evaluate the safety and efficacy of acupuncture as an adjunct treatment for patients with PIGD subtype of PD. Additionally, we will preliminarily explore the mechanisms underlying the therapeutic effect of acupuncture from the perspective of the gut flora-metabolite axis, which will establish a foundation for future research.

## Methods and analysis

2

### Study design

2.1

The study will be a single-center, prospective, randomized controlled trial. The Medical Ethics Committee of Zhejiang Hospital (Hangzhou, China; Approval no. 2023-15K) reviewed and approved the protocol in May 2023, and it was registered at www.chictr.org.cn (ChiCTR2300071703). The study design adheres to the Standard Protocol Items Recommendations for Interventional Trials (SPIRIT).

### Recruitment strategy and consent

2.2

Eligible participants will complete the entire investigation at Zhejiang Hospital. A clinical researcher will thoroughly explain the study objectives and requirements to participants before inclusion. This process ensures that participants have a clearly understanding of the study, and only those who provide written informed consent, personally or through their legal representatives, will be included in the baseline assessment. The trial will consist of a baseline assessment period of approximately lasting 1 week, a 4-week intervention period, and an eight-week follow-up period. Figure 1 illustrates the study flowchart, while Table 1 presents the detailed schedule for participant enrollment, treatments, and assessments.

**Figure 1 fig1:**
[figure not shown]
Flowchart depicting the study protocol. MMSE, Mini-Mental State Examination; UPDRSIII, Unified Parkinson’s Disease Rating Scale III; LED, levodopa equivalent dose; BBS, Berg Balance Scale; rs-fMRI, resting-state functional magnetic resonance imaging.

**Table 1 tab1:** Enrollment, treatment, and assessment schedule.

Period of study	Screening	Baseline week 0	Treatment week 4	Follow-up week 12
Screening of applicants (based on inclusion and exclusion criteria)	✓			
Demographic data	✓			
Baseline evaluation				
• Disease duration	✓			
• Hoehn–Yahr scale	✓			
• MMSE	✓			
• Moca	✓			
• LED	✓			
Informed consent	✓			
Treatment		✓	✓	
Outcome assessment				
• UPDRSIII		✓	✓	✓
• BBS		✓	✓	✓
• Gait analysis		✓	✓	✓
• rs-fMRI		✓	✓	
Sample collection				
• Serum		✓	✓	
• Fecal		✓	✓	
Safety assessment		✓	✓	✓

✓: required; MMSE, Mini-Mental State Examination; UPDRSIII, Unified Parkinson’s Disease Rating Scale III; LED, levodopa equivalent dose; BBS, Berg Balance Scale; rs-fMRI, resting-state functional magnetic resonance imaging.

### Diagnostic criteria

2.3

The diagnostic criteria will adhere to the standards established by the International Movement Disorder Society in 2015 (Berg et al., 2015). Specifically, for the PIGD subtype, the criteria will be fulfilled if the ratio of the mean scores for these disturbances to the tremor score is ≤0.90 (Stebbins et al., 2013).

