### Recruitment criteria

2.4

The following inclusion criteria will be utilized:

(1) A definitive diagnosis of primary Parkinson’s disease according to the standards set by the UK Parkinson’s Disease Society Brain Bank (Demonceau et al., 2015; Hughes et al., 1992). (2) A Hoehn-Yahr level ranging from 1.5 to 3.0 based on the PD grading scale. (3) No restrictions based on sex. The participants must be right-handed and aged between 50 and 85 years (Right-handedness is a standard requirement in fMRI research to ensure consistency in brain hemisphere activation and to minimize confounding variables related to handedness.) (4) Adherence to the western medicine treatment plan for a duration of 3 months or longer, while excluding the use of antibiotics, probiotics, anti-inflammatory drugs, excretory medications, immunosuppressants, acid–base balance medications, and any physical or traditional Chinese medicine treatments (To enhance feasibility, patients were permitted to transition gradually to non-restricted medications under physician supervision before enrollment). (5) The Mini-Mental State Examination (MMSE) and Montreal Cognitive Assessment (MoCA) must indicate that participants exhibit no cognitive impairment. (6) Normal vision, hearing, and language abilities. (7) Participants must provide informed consent and willingly agree to participate.

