### Sample size estimation

2.9

The sample size was determined based on the Unified Parkinson’s Disease Rating Scale (UPDRS) III motor assessment. A previous study (Jang et al., 2020a) provided the sample size estimation. Two-sided two-sample *t-*tests with a significance level of 0.05 were employed to achieve 80% power. The analysis indicated a standard deviation of 1.54 and a mean difference of 1.15 between the two groups. Consequently, the G-Power (v3.1) sample size calculation indicated that each group will consist of 29 patients diagnosed with PIGD-subtype PD, satisfying the inclusion and exclusion criteria. However, to accommodate a 10% attrition rate, the sample size for each group was increased to 32 patients.

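### The PIGD subtype rule in section 2.3 runs in the wrong direction: as written, a worse gait and balance score makes a patient less likely to qualify

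*Protocol article*

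**What the plan says.** The target population is stated consistently. The abstract (Methods) says: "This randomized controlled trial will involve 64 patients diagnosed with the PIGD subtype of PD". Section 2.9 (Sample size estimation) repeats it: "each group will consist of 29 patients diagnosed with PIGD-subtype PD, satisfying the inclusion and exclusion criteria". The Introduction lists the clinical categories of the disease as "including tremor-dominant (TD), postural instability and gait difficulties (PIGD), and the mixed type", so PIGD is set apart from both tremor-dominant and mixed disease.

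The only operational definition of the subtype is in section 2.3 (Diagnostic criteria), with a cited source: "the criteria will be fulfilled if the ratio of the mean scores for these disturbances to the tremor score is ≤0.90". The sentence opens with "Specifically, for the PIGD subtype, the criteria will be fulfilled if the ratio of the mean scores for these disturbances", so the PIGD subtype is the only available antecedent for the disturbances.

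The numbered lists in sections 2.4 (inclusion) and 2.5 (exclusion) give no subtype formula. The first inclusion item begins "A definitive diagnosis of primary Parkinson" and refers to the UK Brain Bank standard, whereas section 2.3 refers to the Movement Disorder Society standard of 2015.

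**The concern.** A rule for selecting patients in whom gait and balance problems predominate should become easier to meet as those problems worsen relative to tremor. The rule in section 2.3 does the reverse: the PIGD score is in the numerator and the patient qualifies when the ratio is small.

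The trial's whole question is about one subtype. If screening followed the sentence as printed, the randomised patients would not be the stated population, and no later analysis could recover it. If screening followed some other rule, readers and anyone replicating the trial would still be given a definition that selects different patients from those studied.

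**Working it through.** **Inputs.** From section 2.3: the ratio, its direction and the cut-off of 0.90. From the abstract, the Introduction and section 2.9: the target population. The cut-off is a stated threshold, so there is no computed figure of the plan's to reproduce. The example scores below are illustrative and are not trial data.

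**Notation.** P is the mean PIGD score and T is the tremor score.

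**Step 1: what the sentence means.** If the disturbances were tremor, the ratio would be tremor over tremor, which is meaningless. The rule is therefore P/T ≤ 0.90.

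**Step 2: direction.** For T > 0, P/T rises with P and falls with T. Worse gait and balance moves a patient away from qualifying; worse tremor moves a patient towards it. This holds whatever the scales of the two scores.

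**Step 3: who qualifies, with both scores on a common scale.** P/T ≤ 0.90 is the same as P ≤ 0.90 × T. Any patient with P ≥ T > 0 has P/T ≥ 1 and fails. With T = 0 and P > 0 the ratio is undefined.

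**Step 4: worked cases**, with the two possible repairs alongside.

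| P | T | P/T | As written (P/T ≤ 0.90) | T/P | Terms swapped (T/P ≤ 0.90) | Inequality reversed (P/T ≥ 0.90) |
|---|---|---|---|---|---|---|
| 2 | 0.5 | 4.0 | rejected | 0.25 | admitted | admitted |
| 1.5 | 1 | 1.5 | rejected | 0.667 | admitted | admitted |
| 1 | 1 | 1.0 | rejected | 1.0 | rejected | admitted |
| 1 | 1.05 | 0.952 | rejected | 1.05 | rejected | admitted |
| 1 | 1.2 | 0.833 | admitted | 1.2 | rejected | rejected |
| 0.5 | 1.5 | 0.333 | admitted | 3.0 | rejected | rejected |
| 0.2 | 2 | 0.10 | admitted | 10.0 | rejected | rejected |
| 1 | 0 | undefined | cannot be classified | 0 | admitted | cannot be classified |

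**Step 5: grid check.** Let P and T each take the 80 values 0.05, 0.10, ..., 4.00, giving 80 × 80 = 6,400 pairs. The written rule admits 2,880 pairs. None of these has P ≥ T, and none also satisfies T/P ≤ 0.90. The printed rule and the swapped-terms rule therefore select populations with no patient in common. The count shows logical separation only; it does not estimate a misclassification rate among real patients.

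**Step 6: the two repairs are not the same rule.** Swapping terms requires P ≥ T/0.90 = 1.11 × T. Reversing the inequality requires P ≥ 0.90 × T. They disagree for patients with P from 0.90 × T up to just under 1.11 × T, such as the third and fourth rows of the table.

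**Step 7: search for a correcting statement.** The abstract, the Introduction, the eligibility lists in 2.4 and 2.5, and section 2.9 give no other subtype formula.

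**The case against.** The best defence is that this is a drafting slip in a journal article that cites a source for its cut-off, and that investigators will have screened with the source's rule. That is plausible, and the article gives no evidence that the printed rule was or will be used at screening. A reader might infer that the trial is enrolling tremor-dominant patients; the document does not support that. The condensed format, however, explains omissions and does not excuse a formula stated in the wrong direction.

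Three further limits stand.

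- A reader might conclude that the right rule must be tremor over PIGD, at most 0.90. The text does not establish this. Keeping the terms and reversing the inequality would also point towards PIGD, and the cited source is not at hand to decide between them.
- A reader might say that the printed rule selects the opposite subtype. The Introduction names a mixed type and the article gives no cut-offs for tremor-dominant or mixed disease, so those who pass could be tremor-dominant or possibly mixed.
- Section 2.3 speaks of mean scores for the disturbances but only of a tremor score. If the two were on different scales, a ratio of 1 would have no special meaning. The direction argument survives; the comparison of P with T needs the common-scale assumption.

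The absence of a subtype item from the list in 2.4, the scheduling of the items needed for the ratio, and the handling of a zero denominator are details an article may leave to the full protocol. The subtype requirement is stated elsewhere in the article. None of these is pressed as a finding.

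**Conclusion.** Wrong as written, and it must be corrected. The rule in section 2.3 contradicts the population named in the abstract and in section 2.9, and nothing in the article overrides it. The direction error follows from the sentence's own arithmetic and needs no outside source.

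The size is conditional. If the rule is applied as printed, with both scores on a common scale, every patient whose PIGD score equals or exceeds the tremor score is rejected, every patient admitted has a PIGD score at or below 0.90 of tremor, and a patient with PIGD and no tremor cannot be classified. How many of the 64 planned patients would be affected cannot be worked out from the article. Nor can it be said which element of the sentence is at fault, or which rule screening uses.

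The two standards named for diagnosing Parkinson's disease, in 2.3 and 2.4, are a separate inconsistency. They neither cause nor worsen the ratio error.

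**What to change.** 1. Check the numerator, denominator and inequality in section 2.3 against the cited source and rewrite the sentence so that it selects PIGD-predominant patients. Swapped terms or a reversed inequality would each point the right way, but they differ for patients with similar scores, so the sponsor must confirm which is meant.
2. State which rule screening has actually used.
3. For anyone already enrolled, recompute the ratio from the item scores and report the subtype mix.
4. Separately, reconcile the diagnostic standard for Parkinson's disease in section 2.3 with the one in section 2.4.

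The cost is a wording amendment to the subtype sentence, a matching edit for the diagnostic standard, and a recheck of item scores for any patient already enrolled. No change to the sample size calculation or the visit schedule follows from this point.

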### Recruitment criteria

2.4

The following inclusion criteria will be utilized:

(1) A definitive diagnosis of primary Parkinson’s disease according to the standards set by the UK Parkinson’s Disease Society Brain Bank (Demonceau et al., 2015; Hughes et al., 1992). (2) A Hoehn-Yahr level ranging from 1.5 to 3.0 based on the PD grading scale. (3) No restrictions based on sex. The participants must be right-handed and aged between 50 and 85 years (Right-handedness is a standard requirement in fMRI research to ensure consistency in brain hemisphere activation and to minimize confounding variables related to handedness.) (4) Adherence to the western medicine treatment plan for a duration of 3 months or longer, while excluding the use of antibiotics, probiotics, anti-inflammatory drugs, excretory medications, immunosuppressants, acid–base balance medications, and any physical or traditional Chinese medicine treatments (To enhance feasibility, patients were permitted to transition gradually to non-restricted medications under physician supervision before enrollment). (5) The Mini-Mental State Examination (MMSE) and Montreal Cognitive Assessment (MoCA) must indicate that participants exhibit no cognitive impairment. (6) Normal vision, hearing, and language abilities. (7) Participants must provide informed consent and willingly agree to participate.

### Exclusion criteria

2.5

Participants will be excluded from the study if they meet any of the following conditions:

(1) A diagnosis of secondary Parkinson’s syndrome or cognitive impairment. (2) Severe hypertension, vascular disease, cardiac insufficiency, or systemic bone and joint diseases that impair walking ability. (3) Contraindications for undergoing fMRI. (4) Receipt of medications such as antibiotics, probiotics, anti-inflammatory drugs, excretory drugs, immunosuppressants, acid–base balance medications, and traditional Chinese medicine within 3 months prior to enrollment (Dethlefsen and Relman, 2011; Palleja et al., 2018). (5) Concurrently participating in other research.

### Dropout criteria

2.6

Participants will be considered to have dropped out of the study if they meet any of the following conditions:

(1) Patients who voluntarily withdraw or do not complete the trial as planned. (2) Inability to continue the study due to adverse events. (3) Patients who discontinue the study early.

### Termination criteria

2.7

The experiment will be terminated if the following conditions are met:

(1) Modifications to PD drug doses. (2) Probiotics and other physical or traditional Chinese medicine treatments are employed throughout the trial. (3) Inability to continue the trial due to serious adverse events. (4) Disease deterioration or serious complications during the trial. (5) Patients are unable to participate in the trial due to other uncontrollable factors.

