#### Primary outcomes

2.15.1

The UPDRS III assesses a patient’s motor function by measuring various aspects, such as language, facial expressions, tremors, rigidity, limb movements, posture, and gait. A lower UPDRS III score indicates a better quality of life (Movement Disorder Society Task Force on Rating Scales for Parkinson’s Disease, 2003). This evaluation will be performed prior to inclusion, 4 weeks post- treatment, and after 8 weeks of follow-up.

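### Section 2.7 ends a participant's trial on deterioration or a PD dose change, so UPDRS III would probably be missing for reasons tied to the outcome itself

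*Protocol article*

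**What the plan says.** All references are to the protocol article.

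- **Section 2.7 (Termination criteria)** opens with "The experiment will be terminated if the following conditions are met". Its list includes "1) Modifications to PD drug doses" and "4) Disease deterioration or serious complications during the trial". The opening speaks of the experiment, but the items describe individual patients; the last reads "Patients are unable to participate in the trial due to other uncontrollable factors".
- **Section 2.6 (Dropout criteria)** counts as dropouts "Patients who voluntarily withdraw or do not complete the trial as planned".
- **Section 2.2** sets out "a 4-week intervention period, and an eight-week follow-up period" after the baseline week.
- **Section 2.15.1** makes UPDRS III the primary outcome, measured before inclusion, at week 4 "and after 8 weeks of follow-up". Table 1 shows the same visits.
- **Section 2.15** asks patients to record their medication, including dose changes, throughout observation.
- **Section 2.9** deals with loss only as a matter of numbers: "to accommodate a 10% attrition rate, the sample size for each group was increased to 32 patients".

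No section says that a participant who meets a 2.7 criterion is still assessed.

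**The concern.** Worsening of Parkinson's disease is largely what a higher UPDRS III score records, and a change of PD dose is commonly a response to motor worsening. A rule that ends participation on either event removes patients after randomisation because of how they are doing on the primary outcome.

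What is at stake is the randomised comparison. If the same worsening threshold applies in both arms and acupuncture works, more sham patients cross it. The sham completers then look better than the full sham arm, and the effect is understated. If the triggers act differently by arm, the bias can go either way. That cannot be excluded, because section 2.8 leaves the practitioners unblinded and section 2.7 does not say who decides that a criterion is met.

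**Working it through.** **1. Does termination end assessment?** The article does not say so outright, so the sections have to be read together. Study treatment lasts 4 weeks and follow-up another 8. The deterioration criterion applies at any time during the trial. In 8 of the 12 weeks there is no study treatment left to stop, so termination can then only mean the end of participation. Section 2.6 classes those who do not complete as planned as dropouts, and no section keeps them under assessment. Ending assessment is therefore the natural reading, though an inferred one. It is firmer for the week 12 score than for the week 4 score.

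**2. The plan's own figure.** Inputs from section 2.9: SD 1.54, difference 1.15, two-sided alpha 0.05, power 80%.

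- Normal approximation: n = 2 × (1.960 + 0.842)² × (1.54/1.15)² = 28.2, so 29 per arm, as stated.
- Exact t-test: 29.14. Power is 0.798 at 29 per arm and 0.837 at 32.
- Attrition: 29 × 1.1 = 31.9, so 32 as stated (29/0.9 = 32.2 would give 33, a trivial difference).

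**3. Illustration of the bias.** The loss rates, the cut-off and the normal model are assumptions; the article gives none of them. A higher score is worse. Sham scores are N(1.15, SD 1.54) and acupuncture scores N(0, SD 1.54), with 32 per arm. Everyone above a common cut-off c is lost, where c = 1.15 + 1.54 × z(1−q) and q is the share of sham lost. With b = (c − μ)/σ and λ = φ(b)/Φ(b), those who remain have mean μ − σλ and SD σ√(1 − bλ − λ²).

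For q = 0.10, c = 1.15 + 1.54 × 1.282 = 3.12:

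- Sham: b = 1.282, λ = 0.195, mean 1.15 − 0.300 = 0.850, SD 1.30, n = 28.8.
- Acupuncture: b = 2.028, λ = 0.052, mean −0.080, SD 1.45, 2.1% lost, n = 31.3.
- Difference: 0.850 + 0.080 = 0.930. Power of the pooled t-test: 0.727.

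In the weaker version, the trigger is a variable correlated 0.5 with the score, so the shift in the mean is 0.5 × σλ and the arms differ on the trigger by 0.5 × 1.15/1.54 = 0.373 SD. The last column is the power if the same numbers were lost at random, which leaves the difference at 1.15.

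| Trigger | Sham lost | Acupuncture lost | Expected difference | Power | Power, same loss at random |
|---|---|---|---|---|---|
| None | 0% | 0% | 1.15 | 0.837 | – |
| Score cut-off | 5% | 0.8% | 1.02 | 0.781 | 0.825 |
| Score cut-off | 10% | 2.1% | 0.93 | 0.727 | 0.812 |
| Score cut-off | 15% | 3.7% | 0.86 | 0.672 | 0.797 |
| Correlation 0.5 | 10% | 4.9% | 1.08 | 0.782 | 0.806 |
| Correlation 0.5 | 15% | 7.9% | 1.06 | 0.755 | 0.788 |

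Simulation of 100,000 trials per row gives 0.777, 0.727 and 0.672 for the three score cut-off rows, so the approximation is adequate.

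**4. Cross-check by overall loss.** Fixing the total lost across both arms instead, a 5% loss splits 8.3% sham and 1.7% acupuncture and leaves a difference of 0.96. A 10% loss splits 15.9% and 4.1% and leaves 0.85, about a quarter below 1.15. Raising N does not change these differences.

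**The case against.** Five points can be made for the plan.

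- **The key step is inferred.** The text does not cancel visits, Table 1 makes no exception for terminated patients, and during weeks 1 to 4 termination could mean only that needling stops. This is fair as far as it goes, and it is why the conclusion is that scores would probably be missing. It does not help in the 8 treatment-free weeks, and a rule that can be read this way still needs the sentence that settles it.
- **Section 2.15 has patients record dose changes throughout observation**, which sits awkwardly with ending observation at a dose change. A medication record is not a UPDRS III assessment, however. It does mean that most of the log needed for the fix already exists.
- **Stable medication is deliberate.** Section 2.4 requires at least 3 months on the western medicine regimen, and an effect under unchanged medication is a legitimate question. But ending assessment does not answer it without bias, and the argument does not cover the deterioration criterion.
- **Analysis populations belong in an analysis plan that is not shown.** Agreed; their absence is not criticised here. Whether a score is collected is a rule of conduct that section 2.7 itself fixes.
- **The magnitude is assumed, and the score cut-off is the harsh case.** This stands. At q = 0.10 the cut-off is only 1.97 points above the sham mean. At q = 0.15 deterioration alone loses 9.4% overall, nearly the whole 10% allowance. With correlation 0.5, selection costs only 2.4 and 3.3 points of power against random loss of the same size. With 3% of sham lost, power is 80.3% under the cut-off and 81.9% under correlation 0.5. Every quantified case understates the effect; none shows a false-positive risk.

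**Conclusion.** The concern holds. Followed as written, section 2.7 loses primary-outcome data for reasons related to the outcome, and the 10% inflation in section 2.9 does not correct that. The mechanism comes from the text, on the reading that termination ends assessment. The size does not come from the text. If 10% to 15% of sham patients are lost, the expected difference falls from 1.15 to 0.93–0.86 when termination follows the score exactly, and to 1.08–1.06 when it correlates 0.5 with it. Power falls from about 84% to 73–67% and to 78–76% respectively. With fewer events or a looser link, the effect is small. Under a common threshold and an effective treatment the bias is towards no effect; with triggers that act differently by arm its direction is open and has not been quantified. This should be fixed, with medium confidence in how much it matters.

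**What to change.** In section 2.7, replace the reference to the experiment with the participant's study treatment, so that the list gives reasons to stop needling and nothing more. Add that the week 4 and week 12 UPDRS III assessments continue for everyone randomised unless consent is withdrawn, and align section 2.6 so that stopping treatment is not by itself dropout. Record each dose change or deterioration with its date, building on the medication record in section 2.15. Analyse as randomised, and keep the participants without such events as a sensitivity analysis.

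The cost is protocol wording and keeping visits that are already scheduled for a few patients; the sample size does not change. The downside is that the main estimate then includes the effect of any dose changes. The event-free sensitivity analysis shows how much that matters, though it carries the selection described above and should not replace the main analysis.
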